## 2. Materials and Methods

### 2.1. Study Design and Population

This protocol was prepared following the Standard Protocol Items: Recommendations for Interventional Trials (SPIRIT) 2025 guidelines, adapted to the extent applicable to the observational prospective design of the present study [23].

Participants will be recruited in the Central Teaching Hospital of the Medical University of Lodz, primary healthcare clinics, and mental health clinics in the Lodz voivodeship. The study population will consist of 60 adults diagnosed with depressive disorders according to the International Classification of Diseases, 11th (ICD-11). Eligible diagnoses will include single-episode depressive disorder, recurrent depressive disorder, and dysthymic disorder, reflecting the spectrum of conditions characterized primarily by depressive symptomatology. Additionally, participants must present with a BDI-II score ≥ 15 at baseline, confirming clinically relevant depressive symptom severity at the time of enrollment.

Each participant will be at the beginning of a new pharmacological antidepressant treatment (5 days before to 5 days after treatment initiation). Antidepressant treatment will not be standardized by the study protocol, as treatment decisions will follow routine clinical practice. Antipsychotic medication used as augmentation of antidepressant treatment will not constitute an exclusion criterion but will be recorded as a combination treatment.

To qualify for the study, participants must meet all inclusion criteria and not meet any exclusion criteria listed in Table 1.

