### 2.6. Statistical Analysis

All analyses will be exploratory and hypothesis-generating. Continuous variables will be summarized using means and standard deviations or medians and interquartile ranges, as appropriate, and categorical variables as counts and percentages. Markedly skewed fatty acid variables may be transformed. Fatty acid measures will be standardized to facilitate comparison of effect estimates. Results will be reported with 95% confidence intervals, and *p*-values will be interpreted in the context of the pilot nature of the study. The primary endpoint will be the change in BDI-II total score from baseline to week 6. Associations between individual baseline fatty acids and depressive symptom trajectories will be examined using separate linear mixed-effects models estimated with restricted maximum likelihood. Repeated BDI-II scores obtained at baseline and at weeks 3, 6, and 12 will constitute the dependent variable. Models will include time, the standardized fatty acid measure, the fatty acid-by-time interaction, age, sex, and antidepressant class as fixed effects, with a participant-specific random intercept. The prespecified primary contrast will represent the association between the baseline fatty acid measure and change in BDI-II score from baseline to week 6. Fatty acids will be analyzed individually rather than entered simultaneously into a single conventional multivariable model.

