Longitudinal changes in DASS-42 subscales and WHOQOL-BREF domain scores will be examined using analogous mixed-effects models. Baseline relationships between fatty acid measures and psychometric variables will be assessed using Pearson or Spearman correlation coefficients, as appropriate. Principal component analysis will be applied to standardized erythrocyte fatty acid variables to identify broader fatty acid patterns and reduce dimensionality. The number of retained components will be determined using parallel analysis and inspection of the scree plot. Component scores will be evaluated in exploratory models analogous to those used for individual fatty acids. PCA will not be applied to the three serum SCFAs. The Benjamini–Hochberg false discovery rate procedure will be used to account for multiple testing involving individual fatty acids. Correction will be applied separately to the primary family of analyses involving the week 6 BDI-II outcome and to each secondary outcome family. Both unadjusted *p*-values and false-discovery-rate-adjusted *q*-values will be reported. Missing follow-up data will be minimized through regular contact with participants and electronic questionnaires requiring completion of all items. The timing and reasons for missed assessments and withdrawal will be recorded. Mixed-effects models will use all available repeated observations and will provide valid estimates under the missing-at-random assumption. Missingness patterns will be examined descriptively, and the potential impact of departures from this assumption will be evaluated in sensitivity analyses if the amount of missing data permits. Missing baseline fatty acid measurements will not be imputed. The study is not designed to establish clinical cut-offs or validate a clinical prediction tool. If an exploratory combined prediction model is developed, its apparent performance and optimism will be assessed using bootstrap resampling. Such findings will require external validation in future adequately powered studies.

Analyses will be performed using Statistica 13.3 and the R software 4.6.1.

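### With a random intercept as the only stated covariance structure, the standard error of the baseline-to-week-6 contrast may be too small or too large

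*Protocol article*

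**What the plan says.** Section 2.6 of the protocol article (Statistical Analysis) specifies, for each fatty acid, "separate linear mixed-effects models estimated with restricted maximum likelihood". On the outcome it says: "Repeated BDI-II scores obtained at baseline and at weeks 3, 6, and 12 will constitute the dependent variable". On the fixed effects: "Models will include time, the standardized fatty acid measure, the fatty acid-by-time interaction", plus age, sex and antidepressant class. The only covariance term named is the one in "with a participant-specific random intercept". The primary contrast is "the association between the baseline fatty acid measure and change in BDI-II score from baseline to week 6".

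The same section sends the resulting p-values through the Benjamini–Hochberg procedure, uses models of the same kind for the DASS-42 subscales and WHOQOL-BREF domains, and states: "Mixed-effects models will use all available repeated observations and will provide valid estimates under the missing-at-random assumption". It mentions no random slope, residual correlation, visit-specific variance or robust standard error, and does not say whether time is categorical.

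Section 2.1 requires a baseline BDI-II of at least 15, described as "confirming clinically relevant depressive symptom severity at the time of enrollment". Section 2.6 also labels all analyses exploratory.

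**The concern.** A random intercept with independent, equal-variance residuals is compound symmetry: the same variance at every visit and the same correlation between any two visits. Several features of the design make exact compound symmetry unlikely. The entry threshold truncates baseline scores but not later ones. Treatment is not standardised and about half the participants are expected to respond, so scores may spread out. The visits are unequally spaced.

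The primary result is one specific difference, week 6 minus baseline. If the model prices it with a variance borrowed from other visit pairs, the 95% intervals and p-values are off, and the q-values built on them inherit the error. The DASS-42 and WHOQOL-BREF mixed models share the structure. The logistic models for response, remission and minimal improvement do not, nor do the baseline correlations.

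**Working it through.** **The plan's own figure.** The article's only derived number is the expected split in section 2.2: 60 × 0.50 = 30 responders and 30 non-responders. It reproduces, but does not bear on this point. No standard deviation, correlation, standard error or power is given.

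**Inputs.** From the article: N = 60, four visits, random intercept, REML, 95% intervals. Assumed: complete data, categorical time, two-sided 5%, and every standard deviation and correlation below.

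**Closed form.** With complete data, the contrast estimate equals the slope of (week 6 − baseline) on the fatty acid. Age, sex and class enter without time interactions, so they drop out of it. Its variances are:

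- true: Var(Y6 − Y0) / Sxx, where Sxx is the fatty acid sum of squares;
- model: 2 × s²(within) / Sxx, where 2 × s²(within) estimates the mean of Var(Yi − Yj) over the six visit pairs.

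Hence ratio = Var(Y6 − Y0) / mean of Var(Yi − Yj). The model SE divided by the true SE is 1/√ratio, and the actual alpha is 2 × [1 − Φ(1.96/√ratio)].

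**Two worked cases**, both with SDs 8/10/11/12. Pair order: 0–3, 0–6, 0–12, 3–6, 3–12, 6–12.

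- All correlations 0.5. Difference variances 84, 97, 112, 111, 124, 133; mean 110.2. Ratio 97/110.2 = 0.88, alpha 3.7%.
- Correlations 0.4, 0.3, 0.3, 0.8, 0.75, 0.8. Difference variances 100, 132.2, 150.4, 45, 64, 53.8; mean 90.9. Ratio 132.2/90.9 = 1.45, alpha 10.4%.

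**Range of assumptions** (simulated alpha from 20,000 runs each, n = 60):

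| Assumed covariance | Ratio | Model SE / true SE | Simulated alpha |
|---|---|---|---|
| Compound symmetry, r = 0.5 | 1.000 | 1.00 | 5.1% |
| Decaying correlation, 0.8 per 3 weeks, equal SDs | 0.983 | 1.01 | 5.0% |
| Equal correlation 0.5, SDs 8/10/11/12 | 0.880 | 1.07 | 3.8% |
| Decaying, 0.7 per 3 weeks, SDs 8/10/11/12 | 0.875 | 1.07 | 3.6% |
| Random slope, SD 0.7 per week (residual SD 6) | 0.917 | 1.04 | 4.0% |
| Random slope, SD 1.0 per week (residual SD 5) | 0.839 | 1.09 | 3.2% |
| Correlations .5,.4,.3,.7,.6,.7; equal SDs | 1.286 | 0.88 | 8.5% |
| Same correlations, SDs 8/10/11/12 | 1.153 | 0.93 | 6.9% |
| Correlations .4,.3,.3,.8,.75,.8; SDs 8/10/11/12 | 1.454 | 0.83 | 10.3% |

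**Effect of the entry threshold alone.** Start from compound symmetry with unit variance and correlation 0.5. Cut the baseline variance to 0.7 and keep the regression of follow-up on baseline linear. Then Var(Yj − Y0) = 0.7 × (1 − 0.5)² + 1 − 0.5² = 0.925, and each follow-up pair has variance 2 × (1 − 0.5) = 1. The ratio is 0.925/[(3 × 0.925 + 3 × 1)/6] = 0.96, alpha 4.6%: mildly conservative.

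**Effect on q-values.** Taking 32 null fatty acids (29 listed reference acids plus three SCFAs), 4,000 runs per scenario gave these chances of at least one q ≤ 0.05, for independent acids and for acids correlated 0.3:

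- compound symmetry: 5.0% and 4.3%;
- the 1.153 case: 9.6% and 8.4%;
- the 1.454 case: 25.6% and 19.9%;
- random slope SD 1.0: 2.2% and 1.6%.

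Using the contrast's own variance, the figure was 4.3% to 5.2% throughout.

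**Dropout.** The article gives no dropout rate. An illustrative large-sample check assumed about 31% dropout after week 3, driven by the week-3 score, and a true contrast of −3. The random intercept returned −2.87 to −2.97, and shifted the mean BDI-II change by 0.3 to 1.2 points. The true covariance recovered −3.

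**The case against.** A reader might infer that the primary standard error, and every q-value in the study, is bound to be wrong, and wrong in the anti-conservative direction. The article does not support that:

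- The standard error is right whenever Var(Y6 − Y0) equals the six-pair mean. That holds under compound symmetry and nearly holds for equal-variance decaying correlation.
- Truncation at entry and rising variances, on their own, make the test conservative. Inflation requires baseline to correlate less with follow-up than follow-up visits do with each other. That is plausible, but the article gives no figure for it.
- The logistic and correlation families do not use this covariance.
- With complete data and categorical time, the effect estimates that the pilot exists to produce are unaffected.

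All of this stands.

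It can also be said that a random intercept does not exclude structured residuals, and that residual covariance, degrees of freedom and fallbacks are often left to an analysis plan. This stands in part. The article is silent on residuals, but it does name a covariance structure, whose ordinary reading is compound symmetry.

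Finally, the work is labelled exploratory, disclaims confirmatory power and attaches no decision rule to p < 0.05. That lowers the severity. It does not remove the point, because 95% intervals and q-values will be reported, and the Discussion presents the effect size and variance estimates as the basis for sizing later studies. Unstructured covariance is one acceptable remedy among several.

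**Conclusion.** The point holds as a risk of miscalibration in either direction. On the ordinary reading of the model, the intervals, p-values and q-values of the BDI-II, DASS-42 and WHOQOL-BREF mixed-model families may be too narrow or too wide. For the primary contrast, actual alpha at a nominal 5% ran from about 3% to 10% over the covariances tried, with the model SE from 17% too small to 9% too large. Sign and size rest wholly on assumed standard deviations and correlations, with complete data and categorical time.

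The missing-at-random sentence is incomplete: with dropout, validity also needs a correctly specified covariance. The bias in the fatty acid association was small in the illustration. Severity: SHOULD-FIX, as a cheap improvement to an exploratory analysis.

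**What to change.** In section 2.6:

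1. State that time is categorical and that the four visits have an unstructured 4 x 4 within-participant covariance, fitted by REML with Kenward–Roger or Satterthwaite degrees of freedom.
2. State the fallback order if the model does not converge: heterogeneous Toeplitz, then the random intercept with small-sample-corrected cluster-robust standard errors.
3. Apply the same specification to DASS-42 and WHOQOL-BREF.
4. Amend the missing-at-random sentence to say that validity also depends on a correctly specified mean and covariance model.

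Cost: a few lines of text and standard software. The unstructured matrix has 10 parameters (4 variances, 6 covariances) against 2 for the random intercept, so eight more to estimate from 60 participants. Intervals may widen slightly.

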During the study, each participant will have a scheduled on-site visit, during which questionnaires will be completed, and blood samples will be collected for analysis. After centrifugation, serum aliquots and washed erythrocyte pellets will be frozen and stored under predefined biobanking conditions. Following this visit, three subsequent time points are planned—at 3, 6, and 12 weeks (follow-up)—during which the participant will receive online questionnaires to complete. Follow-up assessments will be scheduled relative to the date of antidepressant treatment initiation. At each follow-up assessment, participants will report current antidepressant treatment, dose changes, discontinuations, augmentation strategies, newly introduced concomitant medications, and psychotherapy participation. Participants will remain in the study if the antidepressant treatment is modified during follow-up. The type, date, and reason for each treatment modification will be recorded. A sensitivity analysis will be performed after excluding participants with major treatment modifications before the week 6 assessment. The time points’ schedule is also illustrated in Figure 1.

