### 2.3. Scales and Questionnaires

A study questionnaire (SQ) will be used to collect basic socioeconomic data as well as various health-related information. Participants will be asked to provide, among other things, personal details, place of residence, and occupation, as well as information on dietary supplement use, current medications, smoking habits, chronic diseases, and psychotherapy. Use of medications or supplements potentially affecting lipid metabolism, inflammatory status, or gut microbiota composition, including statins, corticosteroids, antibiotics, probiotics, and omega-3 supplements, will also be recorded. For participants receiving antidepressant treatment, the SQ will also record medication class (SSRI, SNRI, or others), dose expressed as fluoxetine equivalents, and use of combination therapy. As most participants will be inpatients at baseline, adherence to antidepressant pharmacotherapy is expected to be high during the initial phase of treatment and will be monitored as part of routine clinical care. Following discharge, participants will be provided with a structured medication adherence form, on which they will be asked to record each administered dose on a daily basis. Completed forms will be collected and reviewed at each subsequent follow-up time point. These variables will be described and, depending on their frequency and data distribution, considered as potential confounders in analyses of treatment response.

Beck Depression Inventory-II (BDI-II) is a widely used self-report questionnaire designed to assess the severity of depressive symptoms in adolescents and adults. The instrument consists of 21 items, each reflecting a specific symptom or attitude related to depression, in accordance with diagnostic criteria for depressive disorders. Respondents are asked to rate how they have been feeling over the preceding two weeks, including the day of assessment. Each item is scored on a 4-point scale ranging from 0 to 3, with higher total scores indicating greater severity of depressive symptoms. The total score ranges from 0 to 63 and is interpreted using established cut-off values: 0–13 indicating minimal, 14–19 mild, 20–28 moderate, and 29–63 severe depressive symptoms [26].

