Antidepressant class will initially be categorized as selective serotonin reuptake inhibitor, serotonin–norepinephrine reuptake inhibitor, or other. Categories may be combined if their sizes do not permit reliable estimation. The robustness of the primary findings will be examined in sensitivity models additionally accounting for relevant dietary, metabolic, lifestyle, and treatment-related factors. These may include fish and seafood intake, a plant- and fiber-rich food index, body mass index or waist circumference, physical activity, smoking, alcohol consumption, comorbidities, concomitant medications, psychotherapy, adherence, hospitalization status, and treatment modifications. Because of the limited sample size, these variables will not all be included simultaneously in a single model. Secondary binary outcomes at week 6 will include treatment response, remission, and minimal clinically important improvement. Their associations with individual fatty acids will be examined using separate exploratory logistic regression models with a limited number of prespecified covariates. Penalized likelihood estimation may be used in the event of complete or quasi-complete separation. 

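### Adherence and treatment modifications arise after the baseline blood sample, so they cannot confound a baseline fatty acid and should not serve as robustness covariates for its week 6 association

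*Protocol article*

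**What the plan says.** The target is set in section 2.6 (Statistical Analysis): "The prespecified primary contrast will represent the association between the baseline fatty acid measure and change in BDI-II score from baseline to week 6". The model is a random-intercept mixed model of BDI-II at baseline and weeks 3, 6 and 12: "Models will include time, the standardized fatty acid measure, the fatty acid-by-time interaction, age, sex, and antidepressant class as fixed effects". Only the fatty acid is interacted with time.

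The same section then says: "The robustness of the primary findings will be examined in sensitivity models additionally accounting for relevant dietary, metabolic, lifestyle, and treatment-related factors". The optional list that follows mixes baseline characteristics (diet, body mass index or waist circumference, smoking) with "concomitant medications, psychotherapy, adherence, hospitalization status, and treatment modifications". It gives no measurement time for any of these and no form of entry. The one stated limit is that "these variables will not all be included simultaneously in a single model".

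On timing:

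- **Adherence.** Section 2.3 has participants keep a daily dose record after discharge, which is collected at the follow-up time points. It then says of these variables that, depending on frequency and distribution, they will be "considered as potential confounders in analyses of treatment response".
- **Treatment modifications.** Section 2.1 records their type, date and reason during follow-up.
- **Psychotherapy and medication.** Two versions exist. The study questionnaire in section 2.3 asks about current medication and psychotherapy. At each follow-up, section 2.1 collects "augmentation strategies, newly introduced concomitant medications, and psychotherapy participation".

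**The concern.** A confounder must precede, or share a cause with, the exposure whose association it distorts. The exposure here is fixed at one blood draw at baseline. What a participant does or is prescribed in the following weeks cannot have influenced it. Those later events can:

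- lie on a path from the fatty acid to the outcome (mediator);
- follow from early improvement or its absence (marker of early response);
- share unmeasured causes with the outcome (collider, if the fatty acid is also linked to them).

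Adjusting for such a variable answers a different question from whether the association survives control of confounding. If the estimate moves, the move cannot be read as confounding removed. If it does not move, that may follow purely from the model form. Either result could be misreported as evidence about robustness.

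**Working it through.** The article gives no effect size, standard deviation or correlation for this point, so there is no plan figure to reproduce. All path values below are assumptions, shown as ranges.

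**1. Time-constant main effect in the stated model.** The fatty acid-by-week-6 contrast is estimated from differences within participants. A covariate that is constant over time, with no time interaction, explains only differences between participants, so with complete data it cannot move the contrast. Single simulated data sets of 60 participants at weeks 0, 3, 6 and 12, fitted by REML with a random intercept, gave:

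| Adherence entered as | Complete data | 15% of follow-up visits missing |
|---|---|---|
| not entered | -3.799 | -2.697 |
| main effect | -3.799 | -2.695 |
| adherence by time | -3.191 | -1.008 |
| time-varying | -3.452 | -1.321 |

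The two columns are different simulated data sets, so compare within a column only.

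**2. Mediation, where the covariate can act on the week 6 change.** Let *a* be the slope of standardized adherence on the standardized fatty acid, *b* the effect of adherence on BDI-II change, and *c* the direct slope, set at -2 points per SD.

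Total association = *c* + *ab*. Adjusted association = *c*. Share removed = *ab*/(*c* + *ab*).

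| *a* | *b* = -2 | *b* = -4 |
|---|---|---|
| 0 | 0% | 0% |
| 0.1 | -0.2/-2.2 = 9% | -0.4/-2.4 = 17% |
| 0.3 | -0.6/-2.6 = 23% | -1.2/-3.2 = 38% |
| 0.5 | -1.0/-3.0 = 33% | -2.0/-4.0 = 50% |

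**3. Marker of early response.** Suppose adherence affects nothing and only follows week 3 improvement. Assume 3 points of improvement per SD of fatty acid at week 6, *s* points per SD at week 3, SD of change 10 at both times, residual week 3 to week 6 correlation *r*, and correlation *ρ* between adherence and week 3 improvement. Then:

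- slope of adherence on the fatty acid: *a* = *ρs*/10
- partial slope of week 6 improvement on adherence: *b* = (*ρ*/10) *r* √(100 - *s*²) √(100 - 9) / (1 - *a*²)
- adjusted association = 3 - *ab*

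Low end (*s* = 1.5, *ρ* = 0.3, *r* = 0.6): *a* = 0.045, *b* = 1.70, *ab* = 0.08. The estimate goes from 3.0 to 2.9, a loss of about 3%.

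High end (*s* = 3, *ρ* = 0.7, *r* = 0.7): *a* = 0.21, *b* = 4.66, *ab* = 0.98. The estimate goes from 3.0 to 2.0, a loss of about 33%.

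No confounding exists in this set-up, so all of the shift is distortion.

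**4. Collider.** Suppose adherence has no effect on outcome but shares an unmeasured cause with it. Take *a* = 0.3, *c* = -2, loading of adherence on the cause ±0.6, and effect of the cause on outcome -1.2. The spurious adherence slope is (-1.2 × ±0.6)/(1 - 0.09) = ∓0.79. The adjusted fatty acid slope is -2 - 0.3 × (∓0.79), which is -1.76 or -2.24. A regression on 400,000 simulated records gave -1.77 and -2.23, against -2.00 unadjusted. The bias therefore runs in either direction.

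**The case against.** The strongest reply is that the sensitivity models extend the stated primary model, in which covariates are plain fixed effects. On that reading an added person-level covariate does not move the contrast at all, and any quoted shrinkage belongs to a model the article does not describe. This stands, and it changes the nature of the defect: on that reading the check is uninformative rather than attenuating. A reader might infer that these models necessarily shrink a real association. The article does not support that, because it does not fix the form of entry and the bias can also run upward.

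Second, a reader might infer that psychotherapy started later and newly added medication will be adjusted for. Section 2.6 does not say so, and baseline versions of both are collected. For these two the defect is only unstated timing.

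Third, the list is optional, all analyses are declared exploratory, and the primary model contains none of these variables. This also stands. A reader might go further and infer that distorted adjusted estimates will be carried into the future study. The article says preliminary estimates will inform that study, but not that sensitivity-model estimates will.

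Fourth, high early adherence is expected because most participants start as inpatients, which may limit its variation. Adherence may also stand in for stable health behaviour, and asking whether an association persists given the drug actually taken is a fair exploratory question. Both are reasonable. They justify a separately labelled analysis, but they do not make a post-baseline record a confounder of a baseline measurement.

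**Conclusion.** The point holds in limited form. Adherence (sections 2.3 and 2.6) and treatment modifications (section 2.6) are post-baseline by the article's own data collection, yet they are treated as potential confounders or robustness adjusters for a baseline predictor. For psychotherapy and concomitant medication the version is not fixed.

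The consequence depends on the model form. It is essentially nil for a time-constant main effect, where the check says nothing. It is a bias of either sign for a covariate-by-time term, a time-varying covariate, or the week 6 logistic models if they use these variables.

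The size cannot be fixed from the documents. Under the assumed paths the loss is 0% to 50% through mediation and about 3% to 33% through early response, and the collider example moves the slope by about 0.23 points either way. The early-response shift of about 0.1 to 1.0 points is smaller than the contrast's sampling SD of about 1.3 points in simulated samples of 60. The harm is thus mainly one of interpretation. This is a cheap and worthwhile correction to an exploratory analysis, and no threat to the primary model.

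**What to change.** **Section 2.6.** Restrict robustness covariates to values fixed at the baseline visit. For the treatment-related items, name hospitalization status at entry, concomitant medication at entry and psychotherapy already in progress at entry. State that each enters with a covariate-by-time term. Without that term, even a true baseline confounder cannot act on the week 6 contrast.

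**Sections 2.3 and 2.6.** Remove adherence, treatment modifications and any follow-up version of psychotherapy or medication from the confounder wording. Report them descriptively, or in separately labelled exploratory analyses of the mediation type, and state that these are not robustness checks.

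**Cost.** Wording only, since all the variables are already collected. There are two downsides. No adherence-adjusted estimate is offered as a robustness result. The interaction terms also use a few more degrees of freedom (three per single-parameter covariate if the four time points are treated as categories), which is a further reason to keep the covariates per model few with 60 participants.

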### 2.2. Sample Size

As this is a prospective pilot study, the planned sample size was not based on a formal confirmatory power calculation. Currently, there is limited data allowing for a reliable estimation of the expected effect size for the association between baseline fatty acid profiles and antidepressant treatment outcomes. Therefore, the planned recruitment of 60 participants was determined pragmatically, based on the feasibility of recruitment, follow-up, and biological sample processing and on the aim of obtaining preliminary estimates of variability, effect sizes, responder proportions, and attrition rates for a future adequately powered study. Based on previous studies, the anticipated treatment response rate is approximately 50% [24]. Therefore, before accounting for attrition, the planned sample of 60 participants may yield approximately 30 responders and 30 non-responders. This estimate is provided to describe the expected sample distribution and does not imply that the study is adequately powered to develop or validate a multivariable prediction model [25].

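### The week 6 logistic models default to ordinary maximum likelihood, which at about 48–60 participants overstates a real log odds ratio by roughly 10–25%; Firth estimation should be the default

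*Protocol article*

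**What the plan says.** Section 1.3 of the protocol article makes three dichotomies of the BDI-II secondary outcomes: response (a fall of at least 50%), remission (a score of 12 or less) and minimal clinically important improvement (a 17.5% fall). Section 2.6 relates each of them at week 6 to the fatty acids, one acid per logistic model, with a small covariate set that it does not name. On estimation it says only: "Penalized likelihood estimation may be used in the event of complete or quasi-complete separation".

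Section 2.2 states that "the planned recruitment of 60 participants was determined pragmatically" and that among the aims are "preliminary estimates of variability, effect sizes, responder proportions, and attrition rates for a future adequately powered study". The Discussion repeats that the estimates should feed sample-size calculations for later cohorts, which are to derive ROC-based thresholds.

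On missing outcomes, Section 2.6 says: "Mixed-effects models will use all available repeated observations and will provide valid estimates under the missing-at-random assumption". It plans sensitivity analyses for departures from that assumption if the amount of missing data permits, and rules out imputing baseline fatty acids. It gives no rule for a missing week 6 binary outcome.

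**The concern.** The maximum likelihood estimate of a log odds ratio is biased away from zero in small samples. The bias grows as the events, or the non-events, become few relative to the number of coefficients. Separation is only its extreme form, where the estimate becomes infinite. A rule that penalises only on separation repairs the infinite estimates and leaves the finite but inflated ones untouched.

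In a confirmatory trial with a fixed test this would matter little. Here the point estimates are themselves a product of the study. Required sample size for a logistic effect scales roughly with 1/(log odds ratio)², so carrying an inflated estimate forward makes the next study too small. A 10% inflation gives 1/1.10² = 0.83 of the size needed (17% too small), and a 25% inflation gives 1/1.25² = 0.64 (36% too small).

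**Working it through.** **The plan's own figure.** There is no power calculation to reproduce: "the planned sample size was not based on a formal confirmatory power calculation". The one figure is the expected split, which follows from the assumed 50% response rate: 60 × 0.50 = 30, in agreement with "the planned sample of 60 participants may yield approximately 30 responders and 30 non-responders" before attrition.

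**Inputs from the article.** N = 60; response rate about 50%; one standardised fatty acid per model; three antidepressant classes.

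**Assumptions, not in the article.** True odds ratio per SD of 1.0, 1.5 or 2.0 (the article says "there is limited data allowing for a reliable estimation of the expected effect size"); covariates age, sex and two class indicators; 48 analysed if 20% are lost; event rates of 30% and 80% besides 50%, to cover outcomes with a stricter or a looser threshold.

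**Simulation.** 3,000 data sets per scenario, each fitted by maximum likelihood (ML) and by Firth. Non-converged or separated ML fits are left out of the ML summary. Relative bias = bias in the log odds ratio ÷ true log odds ratio, with ln 1.5 = 0.405 and ln 2 = 0.693. Results at 50% events:

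| N | True OR | ML: OR (bias in log OR) | Relative bias | SD of log OR: ML / Firth | Firth OR |
|---|---|---|---|---|---|
| 60 | 1.5 | 1.59 (+0.056) | 14% | 0.326 / 0.284 | 1.50 |
| 60 | 2.0 | 2.24 (+0.113) | 16% | 0.385 / 0.327 | 2.01 |
| 48 | 1.5 | 1.65 (+0.095) | 23% | 0.423 / 0.350 | 1.53 |
| 48 | 2.0 | 2.34 (+0.159) | 23% | 0.474 / 0.380 | 2.03 |

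The ORs are geometric means. In these four rows separation or non-convergence occurred in 2% of fits or fewer, so the inflation is not a by-product of separation.

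**Other event rates.** At N = 60, ML gives 1.61–1.62 for a true 1.5 and 2.27–2.30 for a true 2.0. At N = 48 it gives 1.66–1.68 and 2.41–2.46. The N = 48 figures at 80% events leave out the 23–25% of fits that separated or failed, which the plan would allow to be penalised. A second simulation (true log odds ratio 0.50) replaced separated fits by Firth, as the plan permits. In that scenario the mean was 0.62, and 0.62/0.50 = +24%.

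**Fewer covariates.** At N = 60 and 50% events, the second simulation gives 0.55 with age and sex only (+10%), 0.57 with two drug classes (+14%) and 0.59 with three (+18%). With the fatty acid alone and a true odds ratio of 1.5, the first simulation gives a bias of 0.034, and 0.034/0.405 = 8%.

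**No association.** For a true odds ratio of 1.0, ML averages 1.00–1.04.

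**Bias against sampling error.** At 50% events, bias ÷ SD runs from 0.056/0.326 = 0.17 to 0.159/0.474 = 0.34. Coverage of the 95% interval is 94–96% across scenarios.

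**Total error.** For N = 60 and a true odds ratio of 2.0, the root mean squared error is √(0.113² + 0.385²) = 0.40 for ML and √(0.007² + 0.327²) = 0.33 for Firth. Firth lowers both bias and variance.

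**Responder proportion among completers.** With true proportion p, and dropout dR in responders and dN in non-responders, the completer proportion is p(1 − dR)/[p(1 − dR) + (1 − p)(1 − dN)]. Take p = 0.50 and 20% overall dropout (assumed):

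- equal dropout: 50.0%
- non-responders leave twice as often (dR = 0.133, dN = 0.267): 0.4333/0.80 = 54.2%
- dN/dR = 0.67 (dR = 0.240, dN = 0.160): 0.380/0.80 = 47.5%

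The standard error with 48 completers is √(0.25/48) = 7.2 points.

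**The case against.** The strongest reply is that the harm is small. The outcomes are secondary, Section 2.6 calls all analyses exploratory, and results come with 95% intervals whose coverage is nominal. The primary contrast comes from a linear mixed model of continuous BDI-II scores, which this bias does not touch. Penalising only on separation is a common convention. The plan also limits covariates and lets sparse drug classes be combined, which reduces the bias. All of this stands, and it limits the point to a minor one. It does not defend the trigger: Firth costs almost nothing and has the smaller total error, and nominal coverage does not help a planner who carries the point estimate forward.

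Two stronger readings are tempting. A reader might infer that the binary analyses use week 6 completers only and that responder proportions are therefore biased upward. The article does not say the first. It is the likely default of a week 6 logistic model, but the rule may sit in a fuller plan that is not shown. The second depends on who drops out: the completer proportion can be too high, right or too low. The article gives no attrition figure, and Section 2.1 keeps participants whose treatment is modified, so treatment failure alone does not remove them. Dropout that depends only on response status would in any case leave the fatty acid odds ratio essentially unbiased.

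A reader might also infer that using two estimators within one false-discovery-rate family distorts the correction. No such effect has been computed, and it is not claimed here.

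**Conclusion.** The point holds for the choice of estimator and is minor. Under the default that Section 2.6 implies, non-null log odds ratios at 48–60 participants are overstated by roughly 10–25%, with or without separation, and Firth removes nearly all of this. The size rests on assumed odds ratios of 1.5–2.0 per SD, an assumed covariate set, and assumed attrition and event rates. Inflation near 30% appears only at 48 participants with 80% events and with separated fits discarded, which is not what the plan would do. The documents do not support a claim that the responder proportions are biased in a known direction.

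**What to change.** In Section 2.6, replace the conditional sentence with a rule: all week 6 binary models are fitted by Firth penalised likelihood, with profile-likelihood intervals and penalised likelihood-ratio p-values, whether or not separation occurs. The cost is a sentence or two, since R is already planned and has standard packages for this. The downside is slight shrinkage of the estimates. Predicted probabilities are also pulled towards 0.5, so the intercept should be corrected if predictions are reported.

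As an optional sensitivity analysis, multiply impute missing week 6 BDI-II scores from baseline, weeks 3 and 12, the fatty acid and the covariates, then dichotomise. Report the imputed proportions beside the observed ones, without presuming the direction of any difference. Counting missing as non-response is not a neutral substitute: in the three 20% dropout cases above it would turn a true 50% into 38–43%.
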